**12. Suspension/Dropout Criteria**

1) In case of a hemodynamically unstable state before and after anesthesia

2) When a previously undiagnosed patient has an allergic reaction to an anesthetic agent

3) Subject's voluntary withdrawal of consent

4) Failure to follow the instructions of the research doctor

5) Occurrence of a serious disease unrelated to study participation

6) In the case that Your doctor has decided that research is not the best option for participants.

**13. Outcomes and statistical analysis**

1) Primary outcome: Anxiety with APAIS score, Symptom related to anxiety

2) Secondary outcome: Flatus expulsion or defecation time in postoperative time, time of resume feeding, Intra hospital bowel complication, gastric fluid volume & pH, oral secretion at intubation time, QoR 15 score

3) Analysis

All continuous data are compared with Student’s t-test or Wilcoxon’s rank sum test according to normality. All categorical variables are analyzed using the chi-square test, Fisher’s exact test. The descriptive variables will be presented as mean ± standard deviation or median with an interquartile range. The categorical data are summarized as the number (%). The difference in APAIS, the primary outcome will be compared using student’s t-test. The multiple comparisons for sub-scores of APAIS would be adjusted with Bonferroni correction.

The association between QoR-15K and APAIS scores measured in the preoperative holding area will be analyzed using linear regression model.

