**7. Sample size calculation**

1) Primary hypothesis: The anxiety level of the group chewing gum while taking oral carbohydrate drinks during pre-anesthetic fasting will be lower than that of the group taking oral carbohydrate drinks.

2) Based on the results of the previous study, the mean of anxiety measured by VAS immediately before surgery when taking carbohydrate drinks was 34.83, and the standard deviation was 14.8. In addition, in the case of women, it was reported that the average value of anxiety before surgery was about 15% higher. Based on this, the VAS of preoperative anxiety in the female patient group immediately before surgery was corrected to 39.31 ± 17.04. Forty-seven patients in each group are needed to find the difference in the anxiety of 25% between the two groups, with 5% of alpha and power of 80%. Estimating a dropout rate of 10%, a total of 104 patients are needed, 52 in each group.

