**10. Outcomes and assessment**

1) Patient characteristics: Age, sex, height, weight, BMI, ASA class, and other comorbidities,

smoking, alcohol

2) Gastric fluid volume & pH

After taking the right lateral decubitus position, the diameter of the antrum is measured by abdominal ultrasonography.

The gastric fluid volume is calculated using the following formula.

* volume (ml) = 27 + 14.6 9 * antral area (cm²) – 1.289 * age (year)

After anesthesia induction is completed, gastric fluid is collected through an esophageal probe ad acidity is measured using a pH meter.

3) Pre-operative anxiety

(1) Anxiety with VAS

(2) Anxiety with APAIS score

[figure not shown]

The APAIS score was developed to measure patients' anxiety before surgery, and its effectiveness has been verified in several studies. The APAIS score is calculated by summing the scores from 1 to 5 for 6 questions. a

(3) Symptoms related to anxiety

Whether chewing gum during fasting helped to endure the fasting time, difficulty concentrating, and anxiety-related symptoms such as hunger, thirst, dry mouth, fatigue, headache, nausea, etc. were surveyed with a score between 0 and 10 for each item. do. (Questionnaire Attachment 1)

4) Recovery or bowel function

Post-operative nausea & vomiting

Flatus expulsion, defecation time in postoperative time, time of resume feeding

Intra-hospital bowel complication (ileus, dyspepsia, abdominal pain)

5) QoR15

QoR 15 is calculated by the total sum of the patient's postoperative recovery by asking questions on a scale from 0 to 10 for each item. The higher the score, the higher the quality of recovery.

6) Other Observation Items

(1) The amount of oral secretion at the time of intubation (none/ mild/ moderate/ severe)

(2) Total dose of the anesthetic drug used during anesthesia, amount of fluid

(3) Total anesthesia time and operation time

(4) Total amount of opioids used in the intrahospital period

7) Timeline

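### Protocol section 13 contradicts itself on the primary outcome: item 1 lists APAIS and a set of separately scored symptoms, while item 3 treats APAIS alone as primary.

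*Protocol*

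**What the plan says.** Four places in the protocol bear on this point.

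- **Section 13, item 1:** "Primary outcome: Anxiety with APAIS score, Symptom related to anxiety". Two entries, with no statement of how they combine.
- **Section 10, item 3)(3):** the symptom entry is a questionnaire. It opens with "Whether chewing gum during fasting helped to endure the fasting time, difficulty concentrating" and continues with "anxiety-related symptoms such as hunger, thirst, dry mouth, fatigue, headache, nausea, etc". The items "were surveyed with a score between 0 and 10 for each item". The text defines no total and no key item.
- **Section 13, item 3:** "The difference in APAIS, the primary outcome will be compared using" Student's t-test. This is singular and names APAIS only. The one multiplicity provision is "The multiple comparisons for sub-scores of APAIS would be adjusted with Bonferroni correction". The symptom items have no rule of their own, so they fall under the general sentence on continuous data (t-test or rank sum test).
- **Section 7:** the primary hypothesis concerns anxiety only, and the sample size is set for one comparison "with 5% of alpha and power of 80"%.

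The primary objective in section 4 covers both discomfort and anxiety, so it sits closer to item 1 of section 13 than to item 3.

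**The concern.** The primary outcome fixes what counts as a positive trial, and here the same section fixes it in two ways. Under item 3 the trial turns on one APAIS comparison. Under item 1 a symptom score has the same standing as APAIS, and the symptom list is open-ended.

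The choice matters because gum could plausibly change hunger, thirst or dry mouth without changing anxiety. These items are self-reported, and the patients know whether they were given gum. A favourable dry-mouth score with APAIS unchanged could then be presented as a primary result, and item 1 would lend that claim support. Nothing in section 13 limits the error rate across the symptom items, and section 7 allows for only one test.

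**Working it through.** **1. The plan's own figure.** Inputs from section 7: control mean 39.31, SD 17.04, difference 25%, alpha 5%, power 80%.

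- Difference: 0.25 × 39.31 = 9.83, so d = 9.83 / 17.04 = 0.577.
- n per group = 2 × [17.04 × (1.960 + 0.842) / 9.83]² = 47.2.

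The stated 47 is reproduced, apart from rounding, for one two-sided test at 5%. A one-sided test would need 38. The whole 5% is therefore spent on a single comparison.

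**2. Number of primary tests under item 1.** Section 10 names eight items. One asks whether gum helped the patient endure the fast and is not a symptom. The other seven are difficulty concentrating, hunger, thirst, dry mouth, fatigue, headache and nausea. With the APAIS total that makes eight tests. The open end of the list could add more.

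**3. Error rate under each reading.**

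- Item 3 governs, so only the APAIS test decides: 5%.
- Item 1 governs and any of the eight could be claimed as a positive primary outcome, each tested at 5%. Under independence, 1 − 0.95⁸ = 1 − 0.663 = 0.337.
- The same reading with correlated tests, simulated as eight equicorrelated normal statistics, 200,000 draws each, |z| > 1.96:

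| Assumed common correlation | Chance of at least one false positive |
|---|---|
| 0 (exact) | 33.7% |
| 0.3 | 29.8% |
| 0.5 | 25.0% |
| 0.7 | 19.1% |

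The correlations are assumptions; the protocol gives none. Symptoms reported by the same fasting patient are probably positively correlated, so the independence figure is an upper end for eight tests.

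**The case against.** The strongest reply is that the protocol does name a deciding test. Item 3 of section 13 calls APAIS the primary outcome and assigns it one t-test, and section 7 states one hypothesis, about anxiety. On that reading a symptom result could not make the trial positive, and the error rate is 5%. One may add that adjustment among symptom items is commonly left to a statistical analysis plan, and that the questionnaire attachment is not in the text at hand and might define a total.

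Much of this stands, and it rules out three stronger readings that a reader might infer:

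- *That no single test decides success.* Item 3 names one. The defect is a conflict between items 1 and 3, not the absence of a primary test.
- *That the 5% error rate is already lost.* The protocol states no rule that any one significant item suffices. The higher rates apply only if item 1 is used that way.
- *That nine tests give 37%* (1 − 0.95⁹ = 0.370). The arithmetic is right, but the count includes the question about gum's helpfulness, which is not a symptom, and the figure assumes independence.

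The reply does not remove the conflict itself. The protocol, not a later plan, states the primary outcome, and it does so in two incompatible ways. Nor is the symptom entry clearly a slip, because the primary objective in section 4 includes discomfort.

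**Conclusion.** The point holds as an internal contradiction on what is primary, with no rule to settle it. Its size depends on which item governs. The type I error rate is 5% if the APAIS test alone decides. It is about 19% to 34% if APAIS or any of the seven named symptoms could be claimed. That range assumes eight unadjusted tests at two-sided 5%, no true effect on any of them, and a common correlation between 0.7 and 0. It shows the exposure that item 1 leaves open, not a rate that the sponsor planned.

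The contradiction should be resolved before analysis, because it determines what may be reported as the trial's main result. That the sample size in section 7 rests on a VAS rather than on APAIS is a separate point.

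**What to change.** - **Section 13, item 1:** name the APAIS total, measured in the preoperative holding area, as the sole primary outcome, tested at two-sided 5%. This agrees with item 3 and with the anxiety hypothesis in section 7.
- **Section 13, item 2:** move the symptom items to the secondary outcomes, as a closed list. Control them as a family (for example by Holm) or label them exploratory.
- **Section 4:** align the primary objective, which now includes discomfort, with the single anxiety outcome.

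The cost is a few sentences in two sections and no extra patients on account of multiplicity. The downside is that symptom results lose primary status.

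If the sponsor wants symptoms to stay primary, the protocol must define one symptom score and state either an alpha split or a fixed testing order. An equal split (2.5% each) would raise the section 7 requirement from 47 to 58 per group before dropout: 2 × (2.241 + 0.842)² / 0.577² ≈ 57.1, rounded up. This assumes that the section 7 standardised difference applies to both outcomes, which the protocol does not show. A fixed order would keep the first test at 5%.

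### Holm's step-down test could replace plain Bonferroni for the APAIS sub-scores: an optional gain of about 0 to 9 points of power per sub-score, not an error in the plan

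*Protocol*

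**What the plan says.** Section 13 of the protocol gives as "Primary outcome: Anxiety with APAIS score, Symptom related to anxiety". Its analysis paragraph then says "The difference in APAIS, the primary outcome will be compared using student’s t-test", and of the sub-scores: "The multiple comparisons for sub-scores of APAIS would be adjusted with Bonferroni correction".

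Section 10 defines the total: "The APAIS score is calculated by summing the scores from 1 to 5 for 6 questions". The readable text does not say how many sub-scores there are or which questions form each; the scale itself is in a figure that is not shown.

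No significance level is attached to the total or to the sub-score family in section 13, and no order or condition links them. The only level is in the sample size section (section 7), "with 5% of alpha and power of 80" per cent, and that calculation concerns anxiety on a VAS, not APAIS.

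**The concern.** The protocol itself names the adjustment method, so it can be judged as written. Bonferroni compares every one of k sub-score p-values with 0.05/k. Holm compares the smallest with 0.05/k, the next with 0.05/(k − 1), and so on, stopping at the first failure. It holds the family-wise error at 5% under any dependence between the sub-scores, and it rejects whatever Bonferroni rejects. For hypothesis tests, Bonferroni therefore gives up some power and gains no error control in return. What is at stake is how often the trial can show that more than one component of preoperative anxiety responds to gum.

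A second question lies next to it. The sub-scores are built from the same six questions as the total. If the total has its own 5% and the sub-score family another 5%, the error rate across all APAIS tests is not held at 5%.

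**Working it through.** **Inputs from the protocol (section 7).** Control anxiety (VAS) "immediately before surgery was corrected to 39.31 ± 17.04"; sample size "needed to find the difference in the anxiety of 25% between the two groups"; "Forty-seven patients in each group are needed".

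**The plan's own figure.** Difference = 0.25 × 39.31 = 9.83, so d = 9.8275/17.04 = 0.577. Two-sided n per group = 2 × (1.960 + 0.842)² / 0.577² ≈ 47.2. This is 48 if rounded up; the plan states 47. A one-sided 5% test would give 38, so two-sided fits. Power at 47 per group is 79.8% (normal) or 79.0% (t).

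**Inputs assumed.** Two or three sub-scores; the same d on each; equal correlation between them. The protocol gives none of these for APAIS, and d = 0.577 is borrowed from the VAS.

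**Bonferroni power per sub-score.** Noncentrality = 0.577 × √(47/2) = 2.796.
- Two sub-scores, level 0.025: Φ(2.796 − 2.241) = 71.0%.
- Three sub-scores, level 0.0167: Φ(2.796 − 2.394) = 65.6%.

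**Holm, checked by hand for two independent sub-scores.** Holm adds a rejection only when the other sub-score has p below 0.025 and this one lies between 0.025 and 0.05.
- Both move: 0.710 × (0.798 − 0.710) = 0.0625, a gain of 6.3 points.
- Only this one moves: 0.025 × 0.088 = 0.0022, a gain of 0.2 points.

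**Holm by simulation** (200,000 replicates, normal test statistics, 47 per group, d = 0.577 on every sub-score):

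| Sub-scores | Correlation | Bonferroni | Holm | Gain (points) |
|---|---|---|---|---|
| 2 | 0 | 71.0% | 77.3% | 6.3 |
| 2 | 0.5 | 71.0% | 76.1% | 5.2 |
| 2 | 0.7 | 71.0% | 75.8% | 4.7 |
| 2 | 0.9 | 71.0% | 74.8% | 3.9 |
| 3 | 0 | 65.6% | 74.9% | 9.2 |
| 3 | 0.3 | 65.6% | 74.1% | 8.3 |
| 3 | 0.5 | 65.6% | 73.4% | 7.7 |
| 3 | 0.7 | 65.6% | 72.5% | 7.0 |
| 3 | 0.9 | 65.6% | 71.4% | 5.8 |

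(Gains are taken from unrounded simulation output.) A separate simulation of trial data, 20,000 trials per setting at correlation 0.3 to 0.7, agrees: about 70% to 75% with two sub-scores, and 64% to 72–73% with three.

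**Other effects, correlation 0.3 to 0.7.** All sub-scores at d = 0.2 to 0.3: gain 0.8 to 3.4 points. At d = 0.4: 4.4 to 5.6. At d = 0.8: 1.7 to 3.5. If only one sub-score moves: 0.0 to 0.2 (correlation 0 to 0.9).

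**At least one sub-score.** Power is identical, because both methods start with the same comparison. With three sub-scores at correlation 0.5 it is 87.2% for each.

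**Error rate under the global null** (1,000,000 replicates). Within the sub-score family, both methods give 3.0% to 4.9%. For the total at 5% or any sub-score, without a gate:

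| Sub-scores | Correlation 0.3 | 0.5 | 0.7 |
|---|---|---|---|
| 2 | 7.1% | 6.6% | 5.9% |
| 3 | 7.4% | 6.7% | 5.9% |

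The figures are the same for Bonferroni and Holm. Over correlation 0.9 to 0 the range is 5.1% to 8.4%; the bound is 5% + 5% = 10%. With a gate, no sub-score claim can occur unless the total is rejected, so the rate is that of the total, 5%.

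**The case against.** Prespecified Bonferroni is valid and conservative, and the sub-scores are in neither the primary nor the secondary outcome list of section 13. The primary test and the sample size do not depend on them. A reader might infer that the protocol has chosen a wrong method; it has not. This objection stands, and it makes the change optional.

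A reader might also take a gain of 5 to 9 points as established. The documents do not support that, since they give no number of sub-scores and no APAIS effect, SD or correlation. Putting 0.577 SD on every sub-score also implies a larger effect on their sum: with equal variances, 0.577 × √(2/1.3) = 0.72 for two sub-scores at correlation 0.3, and 0.577 × √(3/1.6) = 0.79 for three. If the total has 0.577 instead, Bonferroni power per sub-score falls to 51–63% (two) or 36–54% (three) over correlation 0.3 to 0.7. The Holm gain is then about 5 points (two) or 6 to 7 (three). So the power levels rest on a borrowed figure, but a gain of similar size remains if all sub-scores move. Where one component moves alone, Holm adds almost nothing.

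Holm is not wholly without cost. Bonferroni gives simple simultaneous confidence intervals directly; Holm does not. With Holm tests beside Bonferroni intervals, an interval can include zero for a sub-score that was rejected. This is minor but real.

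Finally, the link between total and sub-scores is partly inference. Section 13 gives no level for the total and no rule that a sub-score result supports a claim when the total fails, and such hierarchy is often left to the SAP, which is not shown. That point also stands.

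**Conclusion.** A small, optional improvement. Holm is never worse than Bonferroni as a test and has the same 5% family-wise control within the sub-scores; that is a mathematical result and needs no assumption about this trial. The size does need assumptions. For two or three sub-scores the gain is about 0 to 9 points each: about 5 (two) or 6 to 9 (three) if all move with d up to 0.577 and correlation 0.3 to 0.7, 1 to 3 for small effects, and near zero if one moves alone.

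A reader might infer that Holm also cures the combined error rate of total and sub-scores. It does not: the 6 to 7% under the global null is the same with either method, and itself rests on taking the 5% of section 7 as the level for the total and on no gate being set elsewhere. Nor do the documents show that an ungated sub-score claim is intended.

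**What to change.** Replace the Bonferroni sentence in section 13 with:

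> *Sub-scores of APAIS will be tested with the Holm step-down procedure at a family-wise 5%.*

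Bonferroni intervals may be shown for description, with a note that an interval can include zero beside a Holm rejection. The cost is one sentence and that note; no patients, data or assumptions are added. It should be settled before unblinding.

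As a separate decision, the sponsor could state that sub-scores are confirmatory only if the APAIS total is significant at 5%. With Holm behind it, this holds the APAIS family at 5%: if the total is truly null, any false claim first needs a 5% error on the total; if the total truly differs, Holm holds the sub-scores at 5%. The price is that a sub-score that moves without the total is reported as descriptive. Either change can be made without the other.

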**4. Study goals and background information**

1) Study goals

(1) Primary objective: This study aims to investigate whether sham feeding with sugar-free gum added to oral carbohydrates during pre-anesthetic fasting would relieve preoperative discomfort and anxiety in a patient undergoing laparoscopic gynecologic surgery.

(2) Secondary objective: Secondary objective is to investigate whether sham feeding with sugar-free gum added to oral carbohydrates during pre-anesthetic fasting would not only relieve preoperative discomfort and anxiety but also promote postoperative bowel function.

2) Rationale & background information

For patients undergoing surgery under general anesthesia, fasting for 6 hours of light meal and 2 hours of clear liquid is required in accordance with the ASA guideline to prevent complications such as gastric fluid regurgitation and pulmonary aspiration. Currently, the ERAS protocol has been introduced for enhanced recovery after surgery in patients undergoing various types of surgery, and it is recommended to allow clear liquids 2 hours before anesthesia and administer carbohydrate drinks during the fasting period. The administration of carbohydrates before surgery can prevent negative effects such as catabolic state and delayed recovery caused by fasting and improve patient satisfaction and well-being sense. The oral carbohydrate recommended to drink 400ml to 800ml up to 2 hours before surgery. The ERAS society suggests that chewing gum during the fasting period before surgery also has a positive effect and can be recommended. We previously studied the anxiolytic effect of chewing gum undergoing gynecologic surgery. (SMC 2019-05-168-001) Chewing gum during preoperative fasting is also thought to facilitate gastrointestinal movements, which will help restore gastrointestinal function. Previous studies have shown that sugar-free gum is not likely to affect the volume and acidity of the stomach immediately after anesthesia compared to patients who did not chew gum, and therefore the risk of regurgitation and pulmonary aspiration is not likely to make a big difference. However, the effect and safety profile of adding chewing gum to oral carbohydrates was not investigated.

We aim to investigate whether sham feeding with sugar-free gum added to oral carbohydrates during pre-anesthetic fasting would not only relieve preoperative discomfort and anxiety but also promote postoperative bowel function.

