**9. Methodology**

1) Time flow

1. The patient is assigned to either the experimental group or control group on a random basis on the eve of the operation. All patients scheduled for gynecologic surgery were instructed to fast overnight before surgery, and oral carbohydrate drink (NO NPO^Ⓡ^: Daesang, Seoul, South Korea) loading was used routinely according to the protocol of the department of gynecology
2. The patients in the control group (CHD group) are requested to follow the aforementioned fasting guideline. The participants were instructed to consume at least 600 mL to 800 mL of carbohydrate drinks up to 3 hours before induction of anesthesia.
3. The patients in the test group (CHD with gum group) follows the fasting protocols of our gynecologic strategy and were encouraged to chew gum freely with oral carbohydrate loading during fasting time.
4. There is no intervention other than chewing gum during fast times between the two groups of patients.
5. Gum will be removed right before being transported to the operating room before transfer. The nurse in charge of the operating room double-checks whether or not gum has been removed during the patient identification process in the preoperative holding area.
6. The severity of anxiety would be examined at the preoperative holding area immediately before surgery.
7. In the operating theater, all participants are provided with supplemental oxygen. During pre-oxygenation, a gastric ultrasound exam is performed by [name].
8. The independent anesthesiologist will induce general anesthesia according to the standardized protocol. Propofol and remifentanil are used using a TCI machine with the aim of a Bispectral Index of 40-60. Blood pressure and heart rate were maintained within 10% of baseline. The blinded anesthesiologist will rate the oral secretion during tracheal intubation.
9. Gastric juice is naturally drained via an esophageal temperature probe (ST probe) during surgery and analyzed with an acidity analyzer.
10. In the course of surgery and maintenance of anesthesia, the subsequent process proceeds without special intervention. Total anesthesia time, operation time, drugs used during anesthesia, and vital signs are collected through medical records. (Attachment of case reporting form)
11. Afterward, the treatment and recovery of patients in the ward will be proceeded according to the general guidelines of the department of obstetrics and gynecology based on the ERAS protocol.

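### The QoR-15/APAIS regression names no arm term although both scores are post-randomisation outcomes; adding arm is a minor, nearly free improvement

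*Protocol*

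**What the plan says.** Protocol section 13, under Analysis, closes with one sentence: "The association between QoR-15K and APAIS scores measured in the preoperative holding area will be analyzed using linear regression model". It names the two scores, the time of the APAIS measurement and the type of model. It does not name covariates, say whether the arms are combined or say which score is the dependent variable.

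Both scores are trial outcomes. On APAIS, the same section says: "The difference in APAIS, the primary outcome will be compared using student’s t-test". Its list of secondary outcomes ends with "oral secretion at intubation time, QoR 15 score". Section 9 places the anxiety measurement after allocation and after the chewing period: "The severity of anxiety would be examined at the preoperative holding area immediately before surgery". The study title (section 1) covers effects of gum on anxiety before surgery and on recovery after it.

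The association between the two scores is not listed among the outcomes in section 13 or the objectives in section 4, so the regression is supportive.

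**The concern.** A regression of one post-randomisation outcome on another can pick up the treatment effect. If gum lowers APAIS and, by some route other than anxiety, raises QoR-15, gum-arm patients will tend to have low APAIS and high QoR-15, and control patients the reverse. Combining the arms without an arm term then gives a negative slope even if, within each arm, anxiety says nothing about recovery.

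At stake is how a secondary message is read. A statement that calmer patients recover better would be partly a restatement of the randomised effect. This can happen only if the trial finds effects on both scores, which is also when such a statement would be most attractive to report.

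**Working it through.** **Inputs.** From section 7: the control VAS anxiety "immediately before surgery was corrected to 39.31 ± 17.04", a 25% difference, alpha 5%, power 80% and 47 per arm. From section 13: the two variables in the model. Assumed, because the protocol does not give them: the gum effects on APAIS and QoR-15 in SD units, and no association within arm.

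**Step 1, the plan's own figure.** The difference is 0.25 × 39.31 = 9.83 points, or 9.83 / 17.04 = 0.577 SD. With two-sided alpha (sidedness is not stated), n = 2 × (1.960 + 0.842)² / 0.577² = 47.2, so 48 per arm. The t-based value is 48.2, so 49. Power at 47 is 0.798. The stated 47 is reproduced within two patients; a one-sided test would need 38. This step supplies only a reference effect and a sample size of 2 × 47 = 94. The protocol gives no figure for the regression.

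**Step 2, the bias.** Write QoR = b × APAIS + c × arm + error, with scores in within-arm SD units and 1:1 allocation. Let gum lower APAIS by dA. Without arm, the fitted slope estimates

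b − c × (dA/4) / (1 + dA²/4).

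With b = 0, c equals the gum effect on QoR-15, dQ, and the induced correlation is

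r = −(dA × dQ / 4) / √[(1 + dA²/4)(1 + dQ²/4)].

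At dA = dQ = 0.577: dA × dQ / 4 = 0.083, so r = −0.083 / 1.083 = −0.077 and R² is about 0.6%.

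**Step 3, chance of p < 0.05 at n = 94.** By Fisher z at 0.577 SD: atanh(0.077) × √91 = 0.73, which gives Φ(0.73 − 1.96) + Φ(−0.73 − 1.96) = about 11%. Simulation (20,000 trials per row, 47 per arm, zero within-arm correlation) agrees:

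| Shift in both scores (SD) | r (formula) | Fisher z, no arm term | Simulated, no arm term | Simulated, arm term |
|---|---|---|---|---|
| 0.3 | −0.02 | 5.5% | 5.6% | 5.1% |
| 0.5 | −0.06 | 8.7% | 8.6% | 5.0% |
| 0.577 | −0.08 | 11.4% | 11.8% | 5.2% |
| 0.8 | −0.14 | 26.3% | 26.4% | 5.0% |
| 1.0 | −0.20 | 49.0% | 50.3% | 5.1% |

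A separate run of 10,000 trials gave 5.2%, 8.1% and 10.9% without arm for the first three rows, and 4.5 to 4.8% with arm.

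**Step 4, unequal effects.** With 0.577 SD on APAIS and 0.3 SD on QoR-15, r is −0.04 and the rate is 6.8%. With 0.577 SD on APAIS and none on QoR-15, r is zero and the rate is 5%.

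**The case against.** The strongest reply is that the protocol never says the arms are pooled or that arm is left out. A reader might infer a rule of pooling without arm; the text supports only that no arm term is mentioned. Covariates of a supportive model are often left to an SAP, and none was available here. This stands, and it limits the point to what the sentence says if followed as written: two variables and nothing else.

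A reader might also infer that the trial hypothesises better QoR-15 with gum, so that success would necessarily create the artefact. The documents do not support this. The formal hypothesis in section 7 concerns anxiety only: "The anxiety level of the group chewing gum while taking oral carbohydrate drinks during pre-anesthetic fasting will be lower". The secondary objective in section 4, that gum "would not only relieve preoperative discomfort and anxiety but also promote postoperative bowel function", concerns bowel function and not QoR-15. The title and the outcome list show that an effect on QoR-15 is under study, but they give no direction or size. Nor is 0.577 SD a planned effect on APAIS or QoR-15, because it comes from VAS figures.

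Third, the protocol promises an association, and an unadjusted slope is a valid description of the association across all participants. If gum improves recovery by lowering anxiety, the arm-driven part is genuine. This is fair as a matter of estimand, but it does not argue against adjustment. If gum acts only through anxiety, c = 0 and both slopes estimate the same b. If c is not zero, only the adjusted slope estimates b under this model.

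**Conclusion.** The point holds as a minor one. Followed as written, the regression lets a between-arm component into the slope whenever gum moves both scores. At 0.577 SD on both, with no within-arm link and 94 patients, the induced correlation is about −0.08 and nominal significance rises from about 5% to 11 or 12%. At 0.3 SD there is almost no inflation. It becomes large (26 to 50%) only at shifts of 0.8 to 1.0 SD. These rates rest on assumed effects, equal for both scores, and on no within-arm association.

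It would go too far to say that a successful trial will show a spurious link between anxiety and recovery: even in the 0.577 SD scenario, about 88 to 89% of trials would show no significant slope. The between-arm APAIS comparison and the sample size are untouched.

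**What to change.** Add one sentence to section 13: QoR-15K will be regressed on holding-area APAIS with randomised arm as a covariate, and the arm-adjusted (within-arm) slope will be reported with its confidence interval. If the overall association is also of interest, show the unadjusted slope beside it and label it as such.

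The cost is one degree of freedom. There is also a slight loss of precision if gum does shift APAIS, because between-arm variation in APAIS no longer informs the slope: at 0.577 SD the standard error rises by a factor of about √1.083 = 1.04. No new data and no change to the sample size are needed.
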